# Efficacy and safety of butylphthalide in secondary prevention of stroke: study protocol for a multicenter, real world trial based on Internet

**DOI:** 10.1186/s12883-022-02815-x

**Published:** 2022-08-19

**Keywords:** Ischemic stroke, Secondary prevention, Butylphthalide, Multicenter, Real-world

## Abstract

**Background:**

As one of the leading causes of morbidity and mortality, stroke and its recurrence has attracted more and more attention. Dl-3-n-butylphthalidle(NBP) has been widely used for treating acute ischemic stroke in China and shows a great clinical effect. NBP plays a role in different pathophysiological processes in the treatment of ischemic stroke, including antioxidants, anti-inflammatory, anti-apoptotic, anti-thrombosis, and mitochondrial protection. Many randomized, double-blind, placebo-controlled, multicenter clinical trials suggest that NBP is a safe and effective treatment for ischemic stroke. To sum up, the current research is mainly focused on the short-term treatment of stroke patients with RCT (randomized controlled trial). Therefore, we designed this study to confirm the role of butylphthalide in secondary stroke prevention in the real world.

**Methods:**

This study will be a multicenter, prospective real-world trial. We would recruit 8000 patients with ischemic stroke from 78 public hospitals in China. All participants will be allocated to one of two parallel treatment groups according to their own wills: (1) butylphthalide group: 0.2 g of butylphthalide capsules three times daily plus routine treatment (aspirin 50-300 mg/d, clopidogrel 75 mg/d, etc.); (2) control group: routine treatment (aspirin 50-300 mg/d, clopidogrel 75 mg/d, etc.). Treatment duration is 90 consecutive days or more. The primary outcome is recurrence rate of stroke within 1 month, 3 months, 6 months and 1 year in butylphthalide group and control group. The secondary outcomes included NIHSS score, the mRS score, other clinical cardiovascular events within one year (sudden death / myocardial infarction / arrhythmia / heart failure, etc.), and adverse events of patients in groups. NIHSS will be captured in the first month after discharge, and the others will be captured at the same time points as the primary end point.

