### Outcomes {12}

#### Primary outcome

##### Recurrence rate of stroke

The proportion of recurrent stroke in patients with ischemic stroke.

Recurrent stroke is defined as a new neurological deficit at least 24 h after the incident stroke according to the World Health Organization definition excluding edema, mass effect, brain shift syndrome or hemorrhagic transformation, and procedure-related strokes [30].

Our researchers will follow up patients and compare the recurrence rate of stroke between the butylphthalide group and the control group at month1, 3, 6 and 12. We will ask the patient’s condition in detail in every follow-up after discharge. If the stroke relapses, the researchers will record the time of recurrence, location of the lesion, TOAST classification, occlusive vessels, sequelae, complications, other diagnoses and related examination results. The researchers will discuss with his doctor in charge to carefully identify whether the patient has a relapse or initial progression.

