### Sample size {14}

The sample size calculation was conducted using the PASS software version 25 (NCSS, LLC. Kaysville, Utah, USA). Previous studies have shown that one-year recurrence rate of stroke patients in China was 17.7% [1]. The underlying assumption was a decline of the recurrence rate of stroke from 17.7% to 14.7%. The sample size of the experimental group and the control group was about 3168 with at least 90% power and an overall two-sided alpha level of 0.05. Taking approximate dropouts of 15% into account, the number of participants recruited was estimated to be 3727 each group. Therefore, 8000 patients will be recruited for this trial.

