## Statistical methods

### Statistical methods for primary and secondary outcomes {20a}

The Kaplan–Meier method is used to draw the survival analysis curve of the percentage of patients with recurrent stroke within 1 month, 3 months, 6 months and 1 year of follow-up. The LogRank method is used to compare the statistical difference in the survival curve between the two groups. The COX proportional regression model is used to calculate the risk ratio (hazards ratios) and 95% CI.

The measurement data (such as NIHSS score and modified Rankin score) is expressed by x ± s, and t-test or Wilcoxon rank sum test is used for comparison between groups. The counting data (such as clinical efficacy and adverse reactions of the two groups) is expressed by chi-square test or Fisher exact test. The subgroup analysis is carried out according to sex, age, medical history and type of stroke.Propensity score matching (PSM) is taken to ensure that the covariates are balanced and comparable. A two-sided *P* value of 0.05 or less is considered statistically significant. All the analyses are done with SPSS software 18.0 or based on R software 3.4.3.

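### Recurrence at 1, 3, 6 and 12 months is all primary with no principal time point named, while the overall alpha of 0.05 and the 90% power are computed for the one-year comparison alone

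*Protocol article*

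**What the plan says.** Four places in the protocol article bear on this.

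- **Abstract, Methods:** "The primary outcome is recurrence rate of stroke within 1 month, 3 months, 6 months and 1 year".
- **Outcomes {12}, Primary outcome:** the researchers will "compare the recurrence rate of stroke between the butylphthalide group and the control group at month1, 3, 6 and 12".
- **Sample size {14}:** the calculation uses a one-year recurrence of 17.7%, assumed to fall to 14.7%, and gives about 3,168 per group "with at least 90% power and an overall two-sided alpha level of 0.05". With 15% dropout this becomes 3,727 per group, and 8,000 are to be recruited.
- **Statistical methods {20a}:** Kaplan–Meier curves cover the four windows, a log-rank test compares the two groups' curves, and a Cox model gives the hazard ratio. The threshold is "A two-sided *P* value of 0.05 or less is considered statistically significant".

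The article does not rank the four time points, divide alpha between them, or say whether one or all of them must reach significance.

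**The concern.** Calling alpha overall is a claim about the whole set of primary comparisons, and the power figure reads as the power of the trial on its primary outcome. Both were derived for one of the four named time points. As the text stands, the primary claim has no defined decision rule: a reader of the results could not tell from this article whether a difference at month 1 with none at month 12 is a positive or a negative trial. The aim is to confirm efficacy, so the rule should be fixed before the data are seen.

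**Working it through.** **1. Reproduce the stated sample size.** Inputs from Sample size {14}: p1 = 0.177, p2 = 0.147, two-sided alpha 0.05, power 0.90, equal groups. Pooled two-proportion formula, with mean rate 0.162:

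n = [1.960 × √(2 × 0.162 × 0.838) + 1.2816 × √(0.177 × 0.823 + 0.147 × 0.853)]² / 0.030²
= (1.0213 + 0.6672)² / 0.0009 = 3,167.8, so **3,168 per group**, as stated. Dropout: 3,168 / 0.85 = 3,727.06, against 3,727 stated. The whole 0.05 is spent on the one-year comparison, and the other three primary time points do not enter.

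**2. Assumptions for the early months.** The article gives no 1-, 3- or 6-month rates, so three shapes are tried. Each is the share of the year's events that has occurred by months 1, 3, 6 and 12:

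- constant hazard: 1/12, 3/12, 6/12, 1
- front-loaded: 0.3, 0.5, 0.7, 1
- very front-loaded: 0.55, 0.7, 0.85, 1

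**3. False-positive rate if any month counts.** The four windows are nested, so the test statistics are correlated: corr(i, j) = √(d_i / d_j) for event counts d_i ≤ d_j. Simulating the four-variate normal under no effect gives the chance of at least one two-sided p ≤ 0.05:

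| Curve | Error |
|---|---|
| constant hazard | 14.8% |
| front-loaded | 12.2% |
| very front-loaded | 10.2% |

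For reference, four independent tests would give 1 − 0.95⁴ = 18.5%, and the Bonferroni bound is 20%. A version with correlations for nested proportions, and with 1-month cumulative rates between about 1.5% and 10%, gives 10.4% to 15.1%.

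**4. Power by month.** Events at one year: 3,168 × (0.177 + 0.147) = 1,026. Hazard ratio: ln(0.853) / ln(0.823) = 0.816, so |ln HR| = 0.203. Power = Φ(|ln HR| × √d / 2 − 1.96), assuming the same hazard ratio throughout.

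Example, month 1 with constant hazard: d = 1,026 / 12 = 85.5, and Φ(0.203 × 9.25 / 2 − 1.96) = Φ(−1.02) = 15%.

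| Curve | Month 1 | Month 3 | Month 6 | Month 12 |
|---|---|---|---|---|
| constant hazard | 15% | 37% | 63% | 90% |
| front-loaded | 43% | 63% | 78% | 90% |

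For the very front-loaded curve at month 1: d = 0.55 × 1,026 = 564, and Φ(0.203 × 23.76 / 2 − 1.96) = Φ(0.45) = 67%.

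**5. What each possible rule delivers.**

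| Rule | Overall alpha | Power |
|---|---|---|
| any month suffices | about 10% to 15% | at least 90% |
| all four months required | at most 5% | no more than month-1 power: 15%, 43% or 67% |
| one test over the year | 5% | 90% |

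Only the last row matches both figures in Sample size {14}, and it is not the primary outcome that the abstract and Outcomes {12} describe.

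**The case against.** The strongest reply is that only one test is planned. Statistical methods {20a} speaks of a log-rank test of the curve and a Cox hazard ratio, and mentions no separate test of recurrence per month. The four months are also the follow-up visits, so they could simply be points read off one curve. The sample size points the same way, since the one-year rate is the only one used. On that reading 0.05 and 90% both hold. This reading is possible and nothing rules it out. But the text does not declare the log-rank test the sole primary test, the sentence before it lists all four windows, and Outcomes {12} plans a comparison at each month.

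A reader might infer the stronger charge that the trial will test four times at 0.05 and claim success on whichever month is significant. The documents do not support that. They state no success rule, and the 0.05 threshold is a general sentence covering the whole section.

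It may also be said that multiplicity adjustment belongs in the statistical analysis plan, which is not shown. That is fair for the mechanics of an adjustment, and no missing alpha split is held against the article here. The choice of primary time point and the alpha and power attached to it are fixed in this article, however, and they do not fit each other.

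Finally, the sizes depend on assumed curves. The Background gives 17.7% recurrence in the first year and over 30% at five years, which suggests falling risk and so favours the front-loaded figures. For that reason a flat statement that the early months are badly underpowered would go too far: the power there depends heavily on the curve. It is also a defect only if those months are primary in their own right.

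**Conclusion.** The point holds in conditional form. The stated overall alpha and power belong to a single one-year comparison, whereas the stated primary outcome has four time points with none named as principal. Under an any-month rule the error is two to three times the stated 5%. That it exceeds 5% does not depend on the curve; its exact size does. Under an all-months rule the 90% power is out of reach for every curve tried. It cannot be concluded that the 5% error rate will in fact be breached, because the one-test reading remains open. What can be concluded is that the article does not show it to be held, and that the decision rule for the primary claim is undefined.

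**What to change.** Name one primary outcome: time to first recurrent stroke over one year, compared once by the planned log-rank test at two-sided 0.05. Make months 1, 3 and 6 secondary, read from the same Kaplan–Meier curve with confidence intervals. Alternatively, test them in a fixed sequence that opens only after the one-year test succeeds. The change affects the wording of the abstract, Outcomes {12} and Statistical methods {20a}. Trial status describes recruitment as ongoing, so the choice can be recorded before analysis.

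The cost is small: no extra data, and 3,168 per group (8,000 recruited) still stands. The downside is that no primary claim can rest on an early month alone.

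Keeping four primary time points would cost more. With Bonferroni at 0.05 / 4 = 0.0125 each, 90% power at one year needs 4,307 per group, or 4,307 / 0.85 = 5,068 after dropout and 10,136 in total, against 8,000 planned. With the planned 8,000 less 15% (3,400 per group), one-year power at 0.0125 would be 80.5%.

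This repair settles multiplicity only. It does nothing about confounding from groups that are self-selected and finally defined by compliance with butylphthalide.

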**Discussion:**

This trial will be exploring the efficacy and safety of butylphthalide in secondary prevention of ischemic stroke to expand the scope of application of butylphthalide soft capsules and provide new ideas for enriching the secondary prevention of stroke.

**Trial registration:**

Chinese Clinical Trial Registry (ChiCTR). Trial registration number: ChiCTR2000034481. Registered on 6 July 2020, http://www.chictr.org.cn/showproj.aspx?proj=55800

**Supplementary Information:**

The online version contains supplementary material available at 10.1186/s12883-022-02815-x.

## Introduction {6}

### Background {6a}

Stroke is a common cerebrovascular disease, which is characterized by high incidence, high disability rate and mortality. Acute ischemic stroke (AIS) accounts for 60% to 80% of stroke. It is a group of clinical syndromes caused by brain tissue blood supply disorder, resulting in ischemic and hypoxic necrosis, and then neurological dysfunction [1]. According to data from the China National Stroke Registry, the recurrence rate of acute stroke patients in China is 17.7% in the first year. The 5-year cumulative recurrence rate exceeds 30% [2]. The American Heart Association Council predicts that another 3.4 million American adults ≥ 18 years of age will have a stroke in 2030. The prevalence rate will increase by 20.5% compared with 2012 [3]. In addition, stroke places a great deal of economic burden on patients, their families as well as the entire society. From 2015 to 2035, the total number of direct medical strokes and related costs are expected to more than double, from $36.7 billion to $94.3 billion [3]. Therefore, how to reduce the recurrence of stroke and improve the prognosis is a hot topic for medical workers all over the world.

NBP has been widely used for treating acute ischemic stroke in China and shows a great clinical effect [4]. According to the Chinese Guidelines for Evaluation and Intervention of Collateral circulation in Ischemic Stroke 2017, interventions for collateral circulation include non-drug interventions, such as external counterpulsation (IIb recommendation, Grade C evidence); and drug interventions, such as NBP (IIa recommendation, Level B evidence) [5]. According to a meta-analysis in 2019, researchers found evidence that the combination of NBP and conventional neuroprotective agents can improve functional recovery 90 days after ischemic stroke compared with traditional drugs alone [6]. NBP is a safe and effective treatment for progressive cerebral infarction (PCI). A randomized, double-blind, controlled study was conducted on the effectiveness and safety of NBP in the treatment of PCI (Zhang et al., 2017). The primary endpoints were the National Institutes of Health Stroke Scale (NIHSS) score before treatment and at 7, 14, 21, and 30 days after treatment, and Barthel Index (BI) evaluation on the 90th day of treatment. The result shows that NBP can improve the prognosis and reduce the burden of daily life of PCI patients [7]. Other randomized, double-blind, placebo-controlled, multicenter clinical trials suggest that NBP may be a safe and effective treatment for ischemic stroke [8–10]. In addition, a Phase II clinical trial of NBP soft capsules for patients with ischemic stroke began in the United States in 2017 (NCT02905565) [5]. To sum up, the current research is mainly focused on the short-term treatment of stroke patients with RCT. Therefore, we designed this study to confirm the role of butylphthalide in secondary stroke prevention in the real world.

### Rationale

NBP was originally extracted from the seeds of Apium Graveolens Linn. It is an effective ingredient of Chinese herbal medicine that used to treat epilepsy [11]. However, it has been found that the effective dose and the toxic dose in treating epilepsy are close, which has a greater safety risk. Therefore, the focus of research has shifted from epilepsy to stroke. Subsequent studies have shown that in the rat ischemic stroke model, NBP can reduce infarct volume, neuronal cell death and brain edema, and preserve the blood–brain barrier [11–17]. A study compared the incidence of stroke, the volume of the brain lesion, patency of the microvessels by FITC-dextran perfusion and the number of microvessels by immunohisochemical detection of vwF between NBP pretreatment group and control group. The incidence of ischemic stroke and the volume of the infarct were decreased, and the perfused microvessels were increased with NBP pretreatment [18]. In addition, NBP reduced glial fibrillary acidic protein (GFAP)-positive astrocytes induced by chronic cerebral ischemia, so as to play a protective effect on hippocampal injury [19]. NBP plays a role in different pathophysiological processes in the treatment of ischemic stroke, including antioxidants, anti-inflammatory, anti-apoptotic, anti-thrombosis, and mitochondrial protection [4, 20]. A study showed that NBP could display strong activity in inhibiting the arachidonic acid (AA)- and adenosine diphosphate (ADP)-induced platelet aggregation in vitro. Furthermore, NBP could release moderate levels of NO and H2S, which would be beneficial in improving cardiovascular and cerebral circulation [21]. Butylphthalide also increases vasodilation and inhibits platelet aggregation [22]. NBP has been confirmed to increases VEGF expression and decreases poststroke inflammation and MMP-9 expression in animal models of stroke [23, 24]. In view of its powerful therapeutic effect on ischemic stroke in animal models, the State Food and Drug Administration of China approved it for clinical trials. The Phase IV clinical research trial was completed in February 2005. NIHSS, Barthel index (BI) and Activities of Daily living scale (ADL) were used as the end points of the study. Total effective rate = (Basic recovery cases + significant improvement cases)^a^ / total number of cases × 100%. And the total effective rate of butylphthalide was 78.2% [25, 26]. A research investigated the effects of dl-3-n-butylphthalide (NBP) on the level of circulating endothelial progenitor cells (EPCs) and clinical outcome in patients with acute ischemic stroke (AIS).The results showed that the levels of circulating EPCs on days 14 and 30 were significantly higher in the NBP group than in the control group. In contrast, NIHSS score was notably lower in NBP group on day 14, 30 and day 90. The mRS score in the NBP group was lower on day 90 [27].

*a:Basic recovery: the score of neurological impairment decreased by 91%-100%, and the degree of disability was 0;*

*Significant progress: the score of neurological impairment decreased by 46% to 90%, and the degree of disability was 1;*

*Progress: the score of neurological impairment decreased by 18% to 45%;*

*No change: the score of neurological impairment decreased or increased by less than 17%;*

*Deterioration: the score of neurological impairment increased by more than 18%.*

### Explanation for the choice of comparators {6b}

Doctors will make medication plans for secondary prevention according to their parents’ condition when they are discharged, and recommend (rather than forcing) them to take butylphthalide. We will manage patients through Internet means such as WeChat Mini Programs, and record their medication regularly. At the end of the whole study cycle, we will take patients who take NBP for 3 months as NBP group, and patients who refused to take butylphthalide or poor drug compliance^b^ as the control group. In addition, we will faithfully record other drugs except butylphthalide soft capsules.

*b:According to the formula: “medication compliance* = *actual number of tablets / number of tablets to be taken* × *100%”, we calculate the patient’s drug compliance. 80% to 120% will be considered as good compliance, while* < *80% or* > *120% will be considered poor compliance.*

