## Trial design {8}

This study is an open-label, noninferiority, two-armed, prospective, multicenter, real world trial conducted at Northwest University in Xi’an, China. The participants will be recruited from 78 hospitals across mainland China. Eligible participants will be assigned to the butylphthalide group or the control group according to their own wills. Every researcher at each study center is scheduled to recruit patients from December 2020 to June 2023. The flow chart of the trial is shown in Fig. 1.

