#### Unblinding and allocation

At the end of the study cycle, the researchers will reveal the actual medication information of the patients, taking patients with good butylphthalide compliance as the butylphthalide group, and patients without taking butylphthalide and patients with poor compliance as the control group, and compare the difference of outcomes between the two groups.

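### The butylphthalide group is defined by 3 months of good intake after discharge while recurrences count from discharge, which biases the primary comparison toward butylphthalide whenever some early recurrers stop

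*Protocol article*

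**What the plan says.** The protocol article defines the groups in two ways.

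- **By wish.** Trial design {8} states: "Eligible participants will be assigned to the butylphthalide group or the control group according to their own wills". The Methods paragraph of the abstract and Sequence generation {16a} say the same in substance.
- **By intake, decided at the end.** Explanation for the choice of comparators {6b} states that, once the study is over, "we will take patients who take NBP for 3 months as NBP group". The control group there is "patients who refused to take butylphthalide or poor drug compliance". Compliance is capsules taken over capsules due, and 80% to 120% counts as good. Unblinding and allocation repeats the rule, "taking patients with good butylphthalide compliance as the butylphthalide group", with "patients without taking butylphthalide and patients with poor compliance as the control group".

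Follow-up visits are timed from discharge (Study setting {9}). For the primary outcome the investigators will "compare the recurrence rate of stroke between the butylphthalide group and the control group at month1, 3, 6 and 12". Section {20a} plans Kaplan-Meier curves, a Cox model and a log-rank test: "The LogRank method is used to compare the statistical difference in the survival curve between the two groups". It adds propensity score matching to balance covariates. It states no landmark and no time-dependent exposure. Section {20c}, on non-adherence and missing data, is marked not applicable.

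**The concern.** The clock starts at discharge, but a patient earns membership of the butylphthalide group only over the following 90 days. Events in those 90 days count toward the primary outcome, and they can also change whether the patient qualifies. Group membership therefore depends partly on the outcome.

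Two mechanisms are at work. A death before day 90 rules out 3 months of intake, which is immortal time in the strict sense. A recurrence followed by reduced intake moves the patient, with the event, into the control group, which is outcome-dependent reclassification. Both remove early bad outcomes from the butylphthalide group. The month-1 and month-3 comparisons lie inside the qualifying window and so use information from after the time they describe.

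At stake is whether a significant primary result could be read as a drug effect at all.

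**Working it through.** **1. The plan's own figure.** For 17.7% v 14.7%, 90% power and two-sided alpha 0.05, with pooled rate 0.162:

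n = [1.960·√(2·0.162·0.838) + 1.2816·√(0.177·0.823 + 0.147·0.853)]² / 0.03² = (1.0213 + 0.6672)² / 0.0009 ≈ 3168 per group.

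3168/0.85 = 3727. Both stated numbers reproduce, so the sample size is not at issue. The planned effect is 3.0 points, a hazard ratio of ln(0.853)/ln(0.823) ≈ 0.82.

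**2. Where a starter ends up under the intake rule.**

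| Course after discharge | Group at study end |
|---|---|
| No event, good intake for 3 months | Butylphthalide |
| Early recurrence, intake stays good | Butylphthalide, with the event |
| Early recurrence, intake falls below 80% | Control, with the event |
| Death before day 90 | Left out or control; the text does not say which |

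Under the grouping by wish, all four stay in the butylphthalide group.

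**3. Size with an inert drug.** Inputs from the document: 17.7% one-year recurrence in everyone, 8000 recruited, 15% dropout (8000 × 0.85 = 6800 analysed), 80% threshold, 90-day course. Assumptions, because the document gives no values: a 3400/3400 split, a constant hazard, and a fraction q of early recurrers who then fail the rule. A fully compliant patient has reached 80% of a 90-day course by day 72, so only recurrers before day 72 are allowed to fail.

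- Hazard: H = −ln(1 − 0.177) = 0.1948 per year.
- Recurrence by day 72: 1 − exp(−0.1948 × 72/365) = 3.77%. By day 90 it is 4.69%.
- Share of starters reclassified: m = q × 0.0377.
- Butylphthalide rate: (0.177 − m)/(1 − m). Control rate if they are moved there: (0.177 + m)/(1 + m).

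| q | Starters moved | Apparent one-year rates | Difference | HR | False-positive rate (simulated log-rank) |
|---|---|---|---|---|---|
| 10% | 13 | 17.4% v 18.0% | 0.6 points | 0.96 | about 8–13% |
| 25% | 32 | 16.9% v 18.5% | 1.6 points | about 0.90 | about 42–49% |
| 50% | 64 | 16.1% v 19.2% | 3.1 points | about 0.81 | about 95% |

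The ranges are the spread over repeated simulations. A hand check agrees. The standard error of the log hazard ratio is about 2/√(6800 × 0.177) = 0.058. The three log hazard ratios are then about 0.7, 1.8 and 3.6 standard errors from zero, giving rejection of roughly 10%, 45% and 95%.

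The difference equals 2m(1 − 0.177)/(1 − m²). Setting it to 0.03 gives m ≈ 0.0182, so q ≈ 0.0182/0.0377 ≈ 48%. At that q an inert drug shows the whole planned effect.

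If the same patients are left out rather than moved, the rates are 16.9% v 17.7% at q = 25% and 16.1% v 17.7% at q = 50%. The false-positive rate is then about 14% and 44%.

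**4. Upper extreme.** A Weibull curve through 17.7% at one year and exactly 30% at five years has shape ln(0.3567/0.1948)/ln 5 = 0.376 and puts 10.9% of patients in recurrence by day 90. Moving recurrers then gives about 50% false positives at q = 10% and near 100% at q = 25%. The Background section says only that the five-year rate is above 30%. A higher figure flattens the curve: an assumed 40% gives 8.1% by day 90.

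**5. Check of the remedy.** In the constant-hazard model, grouping by initiation at discharge gives a mean HR of 1.00 and 4.5% rejection. A day-90 landmark gives 1.00 and 4.7%. The model contains no confounding, so this shows only that the timing bias is removed.

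**The case against.** Several points on the other side stand.

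- **A recurrence does not by itself disqualify anyone.** A reader might infer that the butylphthalide curve is almost event-free for 3 months by construction. It is not: the rule asks for 3 months of intake, not 3 recurrence-free months, so an early recurrer who stays compliant remains in the group with the event.
- **A reader might infer that a significant result is to be expected from an inert drug.** The document does not support that. It does not give q, it leaves management after a new event to the doctor ({11b}), and it describes active measures to keep intake high ({11c}, {18b}). At q = 10% under a constant hazard the false-positive rate is near 10%, not near certainty.
- **Letting every recurrer up to day 90 fail would overstate the size.** With the 80% threshold, day 72 is the fairer cut-off and is used here.
- **The two intake rules are not really in conflict.** Unblinding and allocation omits the 3 months, but the course is set at 90 days or more and the compliance rule is shared. The conflict is with the sections that group by wish.

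Three defences do not stand. An unseen analysis plan cannot excuse the rule, because the rule is stated rather than omitted. A real-world design does not require grouping by later intake. Propensity matching balances covariates and cannot undo a grouping that depends on what happened after discharge.

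**Conclusion.** The concern holds in conditional form. As written, the rule ties group membership to post-discharge intake that a recurrence can change, while events count from discharge. Through this path the bias favours butylphthalide for any q above zero, and it vanishes only if every early recurrer survives and stays compliant.

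The rule can produce a significant benefit from an inert drug. Whether it would do so depends on q and on how early recurrences fall, neither of which the document gives. The constant-hazard figures are the moderate case and the Weibull figures an upper extreme. Deaths before day 90 are not quantified. The contradiction with grouping by wish needs no assumption: a starter who recurs and stops is in one group under Trial design {8} and in the other under {6b}. Because this affects the primary comparison, it should be settled before the analysis.

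**What to change.** Replace the grouping rules in {6b} and in Unblinding and allocation with a single rule consistent with the abstract, {8} and {16a}. Each patient belongs to the group chosen at discharge (butylphthalide accepted or declined), and that choice is recorded on the CRF at that time. All events from discharge count in that group, whatever the later intake. Use this grouping for the primary log-rank and Cox analysis, with the planned propensity matching.

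Keep 3-month good compliers only as a secondary analysis. Use either a day-90 landmark in patients alive and recurrence-free, counting later events only, or butylphthalide as a time-dependent exposure. Make no month-1 or month-3 comparison for them.

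The cost is revised wording, one analysis specification and confirmation that the discharge choice is captured for patients already enrolled. No new patients are needed. The drawback is that the primary estimate will include non-compliers and will look less favourable.
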